## 2. Materials and Methods

### 2.1. Scale and Questionnaires

Study questionnaire (SQ)—this will be used to gather basic information on sociodemographics and data related to health. The participants will be asked to give information on their personally identifying data, diet, nicotine smoking, physical activity, education, living place, professional activity, and whether they are taking dietary supplements and drugs. The personal data will be pseudonymized.

Montgomery–Åsberg Depression Rating Scale (MADRS)—a 10-item, well-validated diagnostic questionnaire used to measure the severity of depressive episodes in patients with mood disturbances. The questionnaire includes questions on the following symptoms: (1) apparent sadness, (2) reported sadness, (3) inner tension, (4) reduced sleep, (5) reduced appetite, (6) concentration difficulties, (7) lassitude, (8) inability to feel, (9) pessimistic thoughts, and (10) suicidal thoughts [42,43].

The 21-item Depression, Anxiety, and Stress Scale (DASS-21)—a 21-item self-administered questionnaire that was designed to measure the magnitude of three negative emotional states: depression, anxiety, and stress. It is assumed that anxiety and stress are two states and can be analyzed separately. Each of the three DASS scales contains 7 items, divided into subscales of 2–5 items with similar content. The depression scale assesses dysphoria, hopelessness, devaluation of life, self-deprecation, lack of interest/involvement, anhedonia, and inertia. The anxiety scale assesses autonomic arousal, skeletal muscle effects, situational anxiety, and subjective experience of anxious affect. The stress scale is sensitive to levels of chronic non-specific arousal. It assesses difficulty relaxing, nervous arousal, being easily upset/agitated, irritable/over-reactive, and impatience. Subjects are asked to use a 4-point severity/frequency scale to rate the extent to which they have experienced each state over the past week. The scores for depression, anxiety, and stress are calculated by summing the scores for the relevant items [44].

WHO Quality of Life-BREF Scale (WHOQOL-BREF)—a well-known 26-item questionnaire that evaluates four domains: physical health, psychological health, social relationships, and environment [45].

Food Frequency Questionnaire (FFQ-6)—a questionnaire designed to assess the consumption of different food groups. Patients are asked to report their “normal consumption” over the past year. We plan to use the Polish self-administered Food Frequency Questionnaire 6 (FFQ-6) by Wądołowska [46].

International Classification of Diseases ICD-11 research criteria for 6A70-73, 6A7Y, 6A7Z [47]—we decided to include the whole of the new category of depressive disorders as the first stage of the eligibility screen in our project (Table 2).

### 2.2. Biological Parameters

Physical examination parameters: blood pressure (BP), weight, body mass index (BMI), and waist circumference (WC). 

We decided to measure waist circumference because central obesity is defined as waist circumference ≥ 94 cm for Europid men and ≥80 cm for Europid women, with ethnicity-specific values for other groups, and it is one of the components of metabolic syndrome diagnosed according to the International Diabetes Federation (IDF) criteria [48].

Blood:

Venous blood will be collected by qualified nurses. The collection will be performed under conditions of fasting after overnight resting in the morning between 8:00 and 10:00 a.m. A complete blood count with differential levels of C-reactive protein, HDL cholesterol, triglycerides, and fasting glucose will be measured in blood serum. The level of oxidative stress will be identified as a ratio of the total antioxidant capacity (TAC) and the level of malonedialdehyde (MDA) will be measured in blood plasma.

To obtain serum for future analyses, the blood will be centrifuged at 1500× *g* for 10 min. The blood samples will be stored in Eppendorf tubes and frozen at a temperature of −80 °C. After utilizing the blood in the experiments, it will be properly disposed of.

Feces:

Each patient included in the study will be asked to collect a sample of feces twice in a specially designed double-sealed bag, which will allow for keeping anaerobic conditions. The subjects will be required not to use laxatives, including mineral and castor oil, and not to consume synthetic fat substitutes or dietary supplements that block fats. It is advisable to wait for 48 h after the administration of a barium enema. The patients will collect stool samples after a night’s rest and deliver them to the investigators. The samples will then be divided into smaller ones and stored at a temperature of −80 °C until further analyses. Fecal short-chain fatty acids (SCFAs), including acetic, propionic, and butyric acids, will be measured with the liquid chromatography–mass spectrometry (LC-MS) technique. To detect potential changes in the composition of microorganisms, we will use 16S ribosomal RNA gene sequencing with a specification of variable regions 3 and 4 (V3–V4). The procedure will be carried out in four stages: (1) DNA isolation involving a qualitative and quantitative evaluation, (2) preparing DNA 16S (V3–V4) library with validation, (3) new-generation sequencing (NGS) on an Illumina 16R V3–V4 rRNA platform with paired-end 2 × 250 pz with fastq files generation, and (4) bioinformatic analysis and preparing a report. Sequences of 16S ribosomal RNA genes will be grouped in operational taxonomic units (OTU) at a similarity cut-off value equal to 97%. 

### 2.3. Ethics

The study will be conducted in compliance with the Declaration of Helsinki. The principal study investigator (PSI) has obtained the consent of the Bioethics Committee of the Medical University of Łódź for the whole protocol (resolution of the Bioethics Committee of the Medical University of Łódź, number RNN/109/20/KE of 28 April 2020). Each participant of the study will receive information on the design and aim of the study in writing. The patient will be included in the study if they meet the inclusion criteria and after they give informed written consent for such an inclusion. The subjects will be informed about the possibility of withdrawing from the study at any stage. There is no risk of negative consequences involved in participation in the study.

### 2.4. Statistical Analysis

Regarding the microbiota composition, we will assess the α-diversity (within-sample diversity and richness using the observed OTUs), β-diversity (diversity of microbial community structure), and taxa abundance. Associations between clinical symptoms severity (according to MADRS and DASS scores) and α-diversity indexes, as well as β-diversity dissimilarities, will be tested using permutational ANOVA (PERMANOVA). Associations between symptoms severity and relative abundances of phyla, genera, and species will be tested using multivariate associations. Models will be multi-adjusted for the covariates: age, dietary variables, BMI, and other confounding factors. The level of significance for statistical tests will be 5%. All statistical analyses will be performed using Statistica 13.3 (StatSoft, Tulsa, OK, USA). 

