The aim of this study was to gather empirical evidence that will enable us to evaluate the impact of probiotic supplementation on the severity of anxiety and depressive symptoms, function and composition of gut microbiota, metabolic parameters, and inflammation and oxidative stress markers in patients with diagnosed depressive disorders.

Our scientific hypotheses were the following:-Comorbidity of anxiety symptoms in patients with diagnosed depressive disorders increases the likelihood of therapeutic response to probiotic supplementation in both depressive and anxiety symptoms;-Metabolic abnormalities, chronic inflammation, and oxidative stress markers may be predictive of probiotic efficacy toward depression;-Probiotic supplementation increases the concentration of fecal short-chain fatty acids and the level of diversity of gut microbiota composition in depressed subjects;-Probiotic supplementation improves metabolic parameters in patients with depressive disorders;-Probiotic supplementation improves inflammation and oxidative stress parameters in patients with depressive disorders;-Functional biomarkers (the ratio of levels of short-chain fatty acids) but not classification (taxonomic) changes of microbiota are typical for depressive disorders.

In our trial, the primary outcome measure will be the severity of depressive symptoms assessed with the Montgomery–Åsberg Depression Rating Scale (MADRS). The secondary outcome measures will include depression, anxiety, and stress symptoms assessed with the Depression, Anxiety, and Stress Scale (DASS) with subscale scores; the quality of life level assessed with the WHOQOL-BREF instrument; blood pressure (BP), body mass index (BMI), and waist circumference (WC) measures; and fasting glucose (fGlc), HDL cholesterol (HDL-C), triglycerides (TG), white blood cell count (WBC), neutrofiles, serum levels of C-reactive protein (CRP), levels of fecal SCFAs, fecal microbiota α-diversity, and the levels of oxidative stress parameters (total antioxidant capacity (TAC) and malondialdehyde (MDA)) in the blood serum (Table 1).

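### PERMANOVA for the association between symptom severity and α-diversity is valid but gives neither a sign nor a confidence interval; a linear model on the same data gives both at almost no cost

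*Protocol article*

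**What the plan says.** Section 2.4 of the protocol article describes α-diversity as a within-sample quantity: "α-diversity (within-sample diversity and richness using the observed OTUs"). Each index therefore gives one number per stool sample.

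The next sentence names the relation to be tested, "Associations between clinical symptoms severity (according to MADRS and DASS scores) and α-diversity indexes", and assigns one method to both kinds of diversity: "α-diversity indexes, as well as β-diversity dissimilarities, will be tested using permutational ANOVA (PERMANOVA"). It then states the adjustment, "Models will be multi-adjusted for the covariates: age, dietary variables, BMI, and other confounding factors", and a 5% significance level.

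The Introduction lists α-diversity among the secondary outcome measures: "levels of fecal SCFAs, fecal microbiota α-diversity, and the levels of oxidative stress parameters". It also states a hypothesis about treatment: "Probiotic supplementation increases the concentration of fecal short-chain fatty acids and the level of diversity of gut microbiota composition in depressed subjects".

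Stool is collected twice per patient (section 2.2), at V1 before the intervention and at V2 after 8 weeks (section 3.2).

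**The concern.** PERMANOVA was built for data that exist only as pairwise dissimilarities between samples. Beta-diversity is of that kind. An α-diversity index is an ordinary scalar response, and turning it into pairwise distances discards the sign of any relation.

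The section thus applies an omnibus test to a named secondary outcome for which a slope could be estimated directly. A significant result would not by itself say whether patients with higher MADRS or DASS scores have richer or poorer microbiota. A non-significant result would come without an interval showing which associations remain compatible with the data. A signed estimate with its standard error is also what a later meta-analysis would need.

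Separately, the relation tested is severity against diversity. The Introduction's hypothesis compares probiotic with placebo, so the test named here does not bear on it.

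**Working it through.** **The plan's own figure.** The article gives no number for α-diversity. Its sample size matters here only because it fixes n. From section 2.4 (Sample Size Calculation), with a difference of 2.9, SD 5.15, two-sided alpha 0.05 and power 80%:

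n per arm = 2 × (1.960 + 0.842)² × 5.15² / 2.9² = 2 × 7.85 × 26.52 / 8.41 = 49.5, so 50 per arm and 100 in total.

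The stated figure reproduces, with power 80.4% at 50 per arm.

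**Step 1: what PERMANOVA returns for a scalar.** Assume one α-diversity value per patient, all 100 patients, Euclidean distance and no covariates. Pseudo-F then equals the ordinary F and R-squared equals r²:

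F = r²(n − 2) / (1 − r²)

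For r = +0.25 and for r = −0.25 (illustrative values): F = 0.0625 × 98 / 0.9375 = 6.53 and R-squared = 6.25%. The output is the same in both cases.

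**Step 2: what an interval adds.** By Fisher's z, atanh(0.25) = 0.255, SE = 1/√97 = 0.102, and 0.255 ± 1.96 × 0.102 gives 0.056 to 0.454. Back-transformed, r lies between +0.06 and +0.43. With the sign reversed it lies between −0.43 and −0.06.

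For a null-looking result, take r = 0.10: F = 0.01 × 98 / 0.99 = 0.99, and 0.100 ± 0.199 back-transforms to about −0.10 to +0.29. The F alone does not show that an association near 0.29 is still compatible with the data.

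**Step 3: simulation check.** Assumed data: 100 patients, observed OTUs centred on 200, residual SD 40, 1,999 permutations, each effect run in both directions.

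| Relation | Signed estimate | PERMANOVA pseudo-F | R-squared | Permutation p |
|---|---|---|---|---|
| OTUs on MADRS | +2.27 per point | 11.72 | 0.107 | 0.001 |
| OTUs on MADRS, reversed | −2.27 per point | 11.72 | 0.107 | 0.0015 |
| Two groups of 50 | +22.0 (t = +3.20) | 10.24 | 0.095 | 0.003 |
| Two groups of 50, reversed | −22.0 (t = −3.20) | 10.24 | 0.095 | 0.003 |

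The two MADRS p-values differ only through random permutation. The identity in step 1 holds: 3.20² = 10.24.

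The linear model also gives intervals. For MADRS, t = √11.72 = 3.42 and SE = 2.27 / 3.42 = 0.66. The 95% interval is 2.27 ± 1.984 × 0.66, about +0.95 to +3.58 OTUs per point, with the signs reversed in the mirror case.

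**Step 4: which question is tested.** Section 2.4 relates MADRS and DASS to diversity. The Introduction's hypothesis concerns the effect of the probiotic. A severity coefficient, signed or not, does not estimate a between-arm difference.

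**The case against.** The strongest defence is that the planned test is sound. The article writes permutational ANOVA, and for a scalar index with Euclidean distance that is a permutation F-test. Every F-test is unsigned, and direction is routinely read from means or slopes reported beside it. The ±0.25 example shows no bias, loss of power or inflated error rate. All of this stands, and it limits the point to one about what is estimated and reported. It does not remove it: once the slope and its interval are reported, the linear model is in effect the analysis and should be the one named.

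A reader might infer more than the documents support:

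- **That PERMANOVA gives no effect size.** It gives R-squared. What is absent is a signed estimate with an interval.
- **That the plan's method cannot support the claim of increased diversity.** That claim is a treatment effect, and section 2.4 does not assign PERMANOVA to the comparison of arms. The between-arm test may stand in a fuller plan that is not shown, so its absence from the article is no finding.
- **That every diversity question in the plan is directional.** Only the probiotic hypothesis states a direction. For severity, section 2.4 speaks of associations, and nowhere does the article predict lower diversity with worse symptoms.
- **That sequencing depth is left uncontrolled**, because "richness using the observed OTUs" tends to rise with read depth. Depth handling may sit in the bioinformatic step of section 2.2 or in the full plan, the adjustment clause is open-ended, and the issue would apply equally to a linear model.

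**Conclusion.** The point holds in a limited form. Section 2.4 names a distance-based omnibus test for a scalar secondary outcome. The test is valid and gives a variance-explained measure. By itself it does not give the direction of the association between severity and diversity, or an interval around it. At n = 100, associations of r = +0.25 and −0.25 are indistinguishable in its output (F = 6.53, R-squared 6.25%), while their 95% intervals do not overlap. It also leaves the hypothesised probiotic effect on diversity unaddressed, because it tests a different relation.

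The equivalence with the ordinary F-test assumes Euclidean distance, and the illustrative figures assume one sample per patient, complete data and no covariates. With covariates the same argument applies to partial correlations on fewer degrees of freedom.

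This is a free improvement: no conclusion of the trial is threatened, and the primary outcome is untouched.

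**What to change.** In section 2.4, restrict PERMANOVA to β-diversity. State that each α-diversity index will be analysed with a linear model on the severity score, using the covariates already named, and that the signed coefficient will be reported with its 95% confidence interval. If non-normality is the reason for a permutation method, take the p-value for that coefficient by permutation.

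For the Introduction's hypothesis, the same model form serves: week-8 α-diversity (V2) regressed on arm and baseline α-diversity (V1). The arm coefficient, with its interval, is the signed probiotic effect.

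The cost is one or two sentences. No visit, sample, assay or sample-size change is needed, because both stool collections are already planned. For the scalar indices, the F-test and R-squared of the planned analysis remain available from the linear model.

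### Species-level association tests ask for finer resolution than 97% OTUs from a V3–V4 16S fragment can reliably give for close relatives

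*Protocol article*

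**What the plan says.** Two sections of the protocol article bear on this.

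Section 2.4 (Statistical Analysis) sets the level of inference: "Associations between symptoms severity and relative abundances of phyla, genera, and species will be tested using multivariate associations". Symptom severity there means the MADRS and DASS scores. The three taxonomic levels are listed together. None is marked as exploratory, and one general significance rule follows: "The level of significance for statistical tests will be 5" per cent.

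Section 2.2 (Biological Parameters, Feces) sets the measurement. The marker and region are given as "we will use 16S ribosomal RNA gene sequencing with a specification of variable regions 3 and 4 (V3–V4"). The reads are "paired-end 2 × 250 pz with fastq files generation". The grouping rule is "Sequences of 16S ribosomal RNA genes will be grouped in operational taxonomic units (OTU) at a similarity cut-off value equal to 97" per cent. The stated purpose is "To detect potential changes in the composition of microorganisms".

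Section 2.4 also uses the OTUs for α-diversity, described as "within-sample diversity and richness using the observed OTUs". That use needs no species names. The article describes no other assay or bioinformatic step that would identify species.

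**The concern.** An OTU at a 97% cut-off is a similarity bin. Its boundary is set by how alike the sequences are over the fragment that was read, and not by where one species ends and the next begins. Closely related species can therefore fall into one bin and share one relative abundance. If a species name is then attached to that abundance, the test is about the bin while the report is about the species.

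Two readings of the results would be at risk:

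- A positive association credited to a named species could belong to a relative in the same bin.
- A null result could partly reflect pooling of relatives whose signals differ. This matters because one hypothesis in the Introduction expects functional markers, and not taxonomic changes, to be typical of depressive disorders. A species-level null could be taken as support for it.

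The Discussion's limitations cover the mixed population, uncontrolled influences on the microbiome and sample size. They do not mention taxonomic resolution. The Introduction's remark that taxonomy alone may be insufficient concerns inferring microbiota function, which is a different matter from telling species apart.

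**Working it through.** The plan gives no figure for taxonomic resolution, so there is none to reproduce. The sample size calculation concerns MADRS and does not enter.

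**Inputs from the documents**

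- Levels tested: phyla, genera and species (section 2.4).
- Region: V3–V4 of the 16S gene (section 2.2).
- Reads: paired-end, 2 × 250 (section 2.2). I take the printed unit to mean base pairs.
- Clustering cut-off: 97% similarity (section 2.2).

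**Assumption**

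The merged fragment length L is not stated. Two reads of 250 give 2 × 250 = 500 bases in total. Merging needs some overlap, so L must be below 500. I use 400 to 480.

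**Formulas**

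- Overlap = 500 − L
- Differences tolerated at the cut-off = (1 − 0.97) × L = 0.03 × L, rounded down to whole bases

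| Assumed L | Overlap | 0.03 × L | Whole bases |
|---|---|---|---|
| 400 | 100 | 12.0 | 12 |
| 420 | 80 | 12.6 | 12 |
| 440 | 60 | 13.2 | 13 |
| 460 | 40 | 13.8 | 13 |
| 480 | 20 | 14.4 | 14 |

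Over this range the tolerance is about 12 to 14 bases, so the result depends little on the assumed length.

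**Which analyses depend on this resolution**

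- Species abundance tests: yes, for species whose fragments differ by no more than roughly this amount.
- Phylum and genus tests: largely not, since pooling close relatives mostly stays within these broader groups.
- OTU-based α- and β-diversity: largely not, since these describe the OTUs themselves.
- Fecal SCFAs: no. They are measured by LC-MS.
- MADRS endpoint and sample size: no.

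**The case against.** The strongest objection is that a 97% cut-off is not a sharp limit. The article does not give the clustering rule. If sequences are compared with a cluster centre, two sequences within 3% of each other can land in different OTUs, and two in the same OTU can differ by more than 3%. If every pair in a cluster must meet the cut-off, a close pair can still be split. This stands: the 12 to 14 bases are an approximate scale and not a threshold below which separation is impossible. It does not restore species identity, because the boundary is still drawn by similarity.

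Second, the article does not say how species names are assigned, and a condensed article may leave the classifier, the reference database and the handling of ambiguous calls to the full protocol. This also stands, and their absence is not the point here. The point is the mismatch between two things that the article does fix: the measurement and the level tested.

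Third, no pair of gut species is shown to merge, and the documents give no sequence distances. So the share of species results affected cannot be stated. A reader might infer that an OTU named after one of the two supplemented species would also contain native relatives. Nothing in the documents shows this, and I do not claim it.

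Fourth, species abundance is a small part of the plan. The outcome list in the Introduction names SCFAs and α-diversity, and Table 1 lists microbiota composition only in general terms. This is right, and it keeps the point minor.

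**Conclusion.** The point holds in a limited form. Section 2.4 puts species on the same footing as phyla and genera, while the measurement in section 2.2 cannot reliably separate close relatives. On an assumed merged length of 400 to 480 bases, the affected species are roughly those differing by up to about 12 to 14 bases. Some associations reported under a species name may therefore belong to a relative.

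A reader might go further and infer that every species result is uninterpretable, or that all pairs within 3% necessarily merge. The documents support neither. Species that differ by more are still separated, and the unstated clustering rule may split some close pairs.

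The conclusion rests on the stated region, read length and cut-off, on the assumed fragment length, and on species abundances being derived from these OTUs, the only sequence grouping that the article describes. The consequence is confined to a supporting association analysis. It is worth correcting because the correction is cheap.

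**What to change.** Either of two changes would do.

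1. In section 2.4, restrict the abundance association tests to phyla and genera. This is a change of wording only. It also gives up results for species that the method could have separated.
2. In section 2.2, replace the 97% OTU clustering with exact sequence variants derived from the same fastq files. Test those variants in section 2.4, and report a species name only where a variant matches a single species, labelled as exploratory. The fragment is no longer than before, so some variants will match several species and must stay unnamed. The α-diversity wording in section 2.4, which counts observed OTUs, would need to be brought into line.

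Neither option needs new samples, new sequencing or anything further from patients. The cost is at most a different bioinformatic step on the same reads, and fewer species-level statements in the report.
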